**Methods:**

The Resilience Coaching for Adolescents with Chronic Musculoskeletal Pain pilot study is an investigator initiated, 2-arm, randomized controlled trial (RCT) of PRISM in the interdisciplinary management of CMP among adolescents. The study will compare usual care versus PRISM+usual care among adolescents newly diagnosed with CMP in the outpatient setting. One caregiver per patient will also be enrolled. The control group will receive usual care with no specific intervention. The treatment arm will receive PRISM, which is a remotely delivered, 1-on-1resilience coaching program, consisting of 4 required skill-based sessions and an optional final session. Sessions will be delivered every 1-2 weeks, lasting about 3 months in total. The primary outcome is the Functional Disability Inventory (FDI) score at 3 months postrandomization. The secondary objectives are to evaluate potential patient- and caregiver-level moderators of PRISM and identify facilitators of and barriers to engagement in PRISM. The estimated sample size is 65 patient-caregiver dyads per group, for a total of 130 dyads.

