**Figure 2 figure2:**
[figure not shown]
PRISM RCT recruitment, screening, and consent process. CHOP: Children’s Hospital of Philadelphia; CMP: chronic musculoskeletal pain; e-consent: electronic consent; EMR: electronic medical record; PRISM: Promoting Resilience in Stress Management; PROMIS: Patient-Reported Outcomes Measurement Information System; RCT: randomized controlled trial.

Those who are not approached at their clinic visit can be contacted retroactively via telephone and, if interested and eligible, can be e-consented via REDCap (Research Electronic Data Capture), a secure, web-based software platform designed to support data capture for research studies [24,25]. For anyone who declines participation, their reasoning is recorded in the study’s master log. Study personnel attempt to contact patient-caregiver dyads a maximum of 3 times before discontinuing recruitment efforts. Once baseline surveys are complete, the dyads will be randomly assigned to a study arm using a 1:1 allocation ratio: PRISM+usual care versus usual care.

Stratified randomization will be implemented by the study statistician in REDCap to ensure a balance in sex (male vs female) and clinic (rheumatology clinic vs interdisciplinary pain [amplified musculoskeletal pain] clinic) between the 2 study arms. The final randomization scheme will be prepared by a statistician independent of the study team to prevent bias. Study staff will not get access to randomization algorithms. Tracking of dyads and randomization will be recorded in the study’s master log.

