Demographics and medical history survey. For the first set of surveys, adolescent participants will be asked whether they have or are currently receiving counseling services and physical therapy, as well as about their exercise routine and whether they perform desensitization exercises.The 10-item Connor-Davidson Resilience Scale (CD-RISC-10) [26] measures the overall sense of resilience, or ability to cope with stressors/challenges, and assesses treatment response. Higher scores (0-40) indicate greater resilience. The CD-RISC-10 has good internal consistency and test-retest reliability.The Benefit Finding Scale for Children (BFSC) [27] is a 10-item measure of benefit finding designed for children. It is a unidimensional measure and has excellent internal consistency reliability. In a sample of children with cancer, small but significant correlations were found with measures of optimism and self-esteem and a negative correlation with trait anxiety [27].The Pain Catastrophizing Scale, Child report (PCS-C) [28] is a validated self-report measure used to assess negative thinking associated with pain. Higher scores reflect higher levels of catastrophic thinking [29].The Children’s Hope Scale [30] measures hopeful thought patterns, or the perception that one’s goals can be achieved. Higher scores indicate greater hopeful thought patterns.The Children and Adolescent Mindfulness Measure (CAMM) [31-33] is a unidimensional measure of mindfulness. Higher scores indicate higher levels of mindfulness. CAMM has good psychometric properties overall.The 8-item Chronic Pain Acceptance Questionnaire Adolescent Short Form (CPAQ-A8) [34] measures pain acceptance using 4 items for each established factor (pain willingness and activity engagement) and is sensitive to treatment. It is correlated with clinically important variables, as its full-length version. Items are scored on a 5-point Likert scale (0=never true to 4=always true). Higher scores indicate more positive perceptions of pain.The Pain Self-Efficacy Scale Child (PSES-C) [35] is a 7-item measure assessing child self-efficacy for functioning normally when in pain. Items are scored on a 5-point Likert scale, with lower scores indicating higher self-efficacy. Initial validation has provided support for the PSES-C’s validity and reliability.The PROMIS (Patient-Reported Outcomes Measurement Information System) Pediatric Global Health 7 (PGH-7) [36,37] is a brief and reliable 7-item summary assessment of a child’s self-reported health. It represents an individual’s overall assessment of their health, focusing on physical, mental, and social health components. The PGH-7 is well understood by children as young as 8 years of age. The measure has test-retest reliability estimates above 0.80, indicating excellent stability. The measure is unidimensional and factor invariant by the age of the child. Raw scores are converted to T-score (SD) values. The mean score is 50 (SD 10).The Functional Disability Inventory (FDI) [38] is a measure of pain-related disability. It is a 15-item measure assessing the degree to which pain interferes with children’s physical functioning over a 2-week period. The FDI has demonstrated adequate psychometric properties in youth with CMP aged 8-18 years [38,39]. The FDI has high internal consistency, moderate-to-high test-retest reliability, and good predictive validity [38-40].The PROMIS Pediatric Numeric Rating Scale v1.0 – Pain Intensity [41] provides a numerical value for self-reported pain intensity experienced by the child in the past 7 days.The PROMIS Pediatric Bank v2.0 – Pain Interference Short Form 8a [41] measures self-reported consequences of pain.The 8-item Patient Health Questionnaire (PHQ-8) [42-46] is a reliable and valid measure of depression severity and a good screening measure in adolescents [43].The 7-item Generalized Anxiety Disorder scale (GAD-7) [47,48] has been demonstrated to be a useful screening measure for anxiety severity in adolescents (11-17 years).The Kessler-6 Psychological Distress Scale (K6) [49,50] is a 6-item scale that measures the level of psychological distress experienced in the past month. It was developed for the US National Health Interview Survey and is currently being used in Canada, Australia, and the rest of the world as part of the World Health Organization’s (WHO) world mental health initiative. The instrument strongly discriminates between community cases and noncases of *Diagnostic and Statistical Manual of Mental Disorders* (DSM)-IV psychiatric disorders, such as serious emotional distress or serious mental illness (area under the curve [AUC]=0.74-0.88) [51]. The K6 has been extensively cross-validated, including among adolescents and parents. Responses are scored on a 5-point Likert scale (total score ranging from 0 to 24). Previous studies have shown that scores≥7 are consistent with high distress, and scores≥13 meet the criteria for serious or debilitating psychological distress [49].The Pain and Symptom Assessment Tool (PSAT) [52] is a modified version of the 2010 American College of Rheumatology (ACR) criteria for fibromyalgia (FM) syndrome, which has demonstrated good specificity and sensitivity for the diagnosis of juvenile FM in adolescents [53]. The PSAT consists of 2 components: the Widespread Pain Index (WPI) and the Symptom Severity (SS) checklist. The WPI is a questionnaire that identifies pain in the past week in 19 body locations (score 0-19). The SS checklist comprises 2 components that identify the severity of cardinal symptoms on a scale from 0 (no problem) to 3 (severe problem) and the presence or absence of associated somatic symptoms. A score is assigned based on the overall number of symptoms (0-3: 0=none to 3=a great deal of symptoms). A final SS score is calculated by adding the cardinal symptoms’ scores to the somatic symptoms’ checklist scores (maximum score=12). According to the adult ACR FM criteria, a score of ≥5 and a WPI of ≥7 or an SS score of ≥9 and a WPI of 3-6 indicates a positive diagnosis for juvenile FM.The Acceptability of Intervention Measure (AIM), the Intervention Appropriateness Measure (IAM), and the Feasibility of Intervention Measure (FIM) [54,55] are 4-item measures of implementation outcomes that are often considered leading indicators of implementation success. With readability at the fifth-grade level, these measures can be administered to a wide range of stakeholders to determine the extent to which they believe an intervention or an implementation strategy is acceptable, appropriate, and feasible. The IAM items can be modified to specify a referent organization, situation, or population. Cutoff scores for interpretation are not yet available; however, higher scores indicate greater acceptability, appropriateness, and feasibility. The AIM, IAM, and FIM have demonstrated strong psychometric properties. Specifically, the measures have demonstrated content validity, discriminant content validity, reliability, structural validity, structural invariance, known-groups validity, and responsiveness to change. The predictive validity of the measures is currently being evaluated.Satisfaction with PRISM. Session-specific and overall intervention satisfaction will be measured via a 5-point Likert scale (1=very dissatisfied to 5=very satisfied). The intervention will be defined as acceptable if the mean level of satisfaction (including session-specific and overall intervention satisfaction) is ≥3.

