#### Quantitative Data

Quantitative measures will be used to assess the primary and secondary efficacy outcomes, moderators of PRISM, and implementation outcomes. Demographics and baseline clinical characteristics will be summarized by standard descriptive summaries (eg, means and SDs for continuous variables, such as age, and percentages for categorical variables, such as gender). The primary analysis will use an intention-to-treat (ITT) approach to mitigate confounding from nonrandom participant attrition. We anticipate a total of 100 evaluable subjects. To ensure valid randomization, we will assess demographic and clinical features, along with baseline measures of outcomes, such as physical function, pain intensity, and psychological distress, and compare the intervention to the control arm. The primary outcome will be functional disability (FDI score) assessed at the end of the intervention (month 3). The key predictor is PRISM. Secondary outcomes will include the FDI score at the conclusion of the observation period (month 9, 6 months postintervention) and psychological distress (K6 total) and pain intensity (PROMIS Pediatric Numeric Rating Scale v1.0 – Pain Intensity) at both 3 and 9 months.

Assuming balanced arms postrandomization, we will evaluate the differences in clinical outcomes between the 2 arms at months 3 and 9 using 2-sample Student *t* tests. Longitudinal changes from month 3 to month 9 will be assessed using MANOVA (multivariate analysis of variance) and linear mixed effects models to account for within-subject correlation due to repeated measures. The linear mixed effects model can additionally adjust for a few known prognostic covariates, such as fulfillment of criteria for juvenile FM. Similar analyses will examine outcomes of psychological distress and pain intensity separately.

Linear regression will be conducted to assess the association between the change in FDI scores and changes in the intervention targets, adjusted for baseline covariates of interest. These analyses will be repeated to examine correlations between changes in secondary outcomes (pain intensity and psychological distress) and hypothesized intervention targets at month 3, and we will conduct multivariable linear regression models, adjusting for covariates of interest.

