Furthermore, we will explore adolescent- and caregiver-level moderators of intervention effects, guided by an intersectionality framework [59]. For instance, we will investigate whether age moderates the intervention’s impact on functional disability by including the age × intervention interaction in the linear mixed effects regression model. If the interaction is significant, we will interpret it by plotting simple regression lines for younger (12-14 years) and older (15-16 years) adolescents. If PRISM proves more beneficial for younger participants, future studies may focus on this age group to maximize intervention effects. Additionally, we will evaluate whether biological sex moderates the intervention’s impact, ensuring adequate inclusion of male participants, given the predominance of females in the population with CMP [60].

Analyses will include calculation of eligibility, recruitment and attrition rates, and power considerations for the future full-scale RCT and evaluation of treatment fidelity. We will report the number of eligible subjects approached, the proportion of those subjects enrolled in the study, and the mean percentage of required sessions (PRISM 1-4 sessions + “coming together” session) attended among enrolled subjects. The study will be defined as feasible (binary) if the recruitment rate is ≥60%, the completion rate of all sessions among enrolled subjects is ≥70%, and the mean FIM score is ≥4. The intervention will be acceptable and appropriate if the mean AIM and IAM scores are ≥4 each. Intervention satisfaction (including session-specific and overall intervention satisfaction) will be reported as mean scores from the 5-point Likert scale (1=very dissatisfied to 5=very satisfied).

With a sample of 130 patient participants and an assumed ~20% attrition rate, we have more than 80% statistical power to detect a difference down to 5 points in the FDI between the intervention and control arms, given a prespecified mean FDI score of 26.9 (SD 11.8) and a significance level of .05 for the Student *t*-test. Table 1 lists the detectable differences (DDs) for the outcomes of interest, as well as the minimal clinically important difference (MCID) for each measure. The effect sizes of CBT on the FDI in similar patient populations have been strong to moderate (0.8-0.9), with between-group differences in the FDI score of 5.39 (95% CI 1.57-9.22). Therefore, we will be adequately powered for the primary outcome [61,62].

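### PRISM counts as acceptable at a mean satisfaction of 3, the midpoint of the 1–5 scale, and this rule is not reconciled with the stricter AIM/IAM rule in the analysis section

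*Protocol article*

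**What the plan says.** Two places in the protocol article define when PRISM is acceptable.

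- Medical Record Review and Questionnaires, item on satisfaction with PRISM: patients rate each session and the whole programme on a five-point scale, of which only the two end categories are labelled. The rule follows: "The intervention will be defined as acceptable if the mean level of satisfaction (including session-specific and overall intervention satisfaction) is ≥3".
- Statistical Analysis, Quantitative Data: "The intervention will be acceptable and appropriate if the mean AIM and IAM scores are ≥4 each". The next sentence gives satisfaction no threshold: "Intervention satisfaction (including session-specific and overall intervention satisfaction) will be reported as mean scores from the 5-point Likert scale".

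Neither place refers to the other. Each is worded as a condition that is enough by itself, and nothing says which one decides or whether both are required.

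**The concern.** Acceptability is named in the objective of the pilot, and the abstract's conclusions present it as something the trial will demonstrate to inform a larger multisite trial. The satisfaction rule compares a bare sample mean with the middle of the scale. If half the patients score 2 and half score 4, the mean is 3.0 and the rule is met, although as many patients lean towards dissatisfaction as towards satisfaction. A pass on this rule therefore says little about whether patients liked the programme.

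The analysis section uses the same word with a cutoff of 4 on other instruments. With both rules in print and no order between them, the two could disagree, and a report could rest on the easier one.

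**Working it through.** The article states no error rate for the satisfaction rule, so there is no figure to reproduce. The check evaluates the rule as worded.

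**Inputs from the article**

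- Scale 1 to 5, so the midpoint is (1 + 5)/2 = 3. The label of category 3 is not given; reading it as neutral is an inference from the symmetric end labels.
- Arm size: "The estimated sample size is 65 patient-caregiver dyads per group, for a total of 130 dyads".
- Evaluable patients: "We anticipate a total of 100 evaluable subjects". Allocation is "using a 1:1 allocation ratio: PRISM+usual care versus usual care", which gives 100/2 = 50 in the PRISM arm. The number of satisfaction raters is not stated; 50 to 65 is taken as the range.

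**Assumed, because the article does not give it**

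- The spread of satisfaction ratings: SD 0.5 to 1.2 in the normal approximation, and five rating distributions with SD 0.65 to 1.82 in the exact calculation.
- One score per patient.
- AIM and IAM means on a 1–5 scale.

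**Step 1. True mean exactly 3.0.** The normal approximation is P(pass) = 1 − Φ((3 − μ)/(SD/√n)). With μ = 3 this is 1 − Φ(0) = 0.50 for any SD and n. The exact probability is P(sum of n ratings ≥ 3n), obtained by convolving the rating distribution n times. It is slightly higher because a tie at 3 counts as a pass. The last column applies the same calculation to a cutoff of 4 (step 3).

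| Percent rating 1/2/3/4/5 | SD | Mean ≥3, n = 50 | Mean ≥3, n = 65 | Mean ≥4, n = 50 |
|---|---|---|---|---|
| 20/20/20/20/20 | 1.41 | 0.5199 | 0.5175 | 1.9×10⁻⁷ |
| 10/20/40/20/10 | 1.10 | 0.5257 | 0.5226 | 3.8×10⁻¹¹ |
| 2/13/70/13/2 | 0.65 | 0.5438 | 0.5383 | 2.2×10⁻²³ |
| 40/5/10/5/40 | 1.82 | 0.5155 | 0.5136 | 4.2×10⁻⁵ |
| 5/35/25/25/10 | 1.10 | 0.5235 | 0.5207 | 8.4×10⁻¹¹ |

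The pass probability is 0.51 to 0.54 throughout.

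**Step 2. True mean 2.9.** At n = 50 and SD 1.0, the standard error is 1.0/√50 = 0.141 and z = 0.1/0.141 = 0.707, so P(pass) = 0.240. Results over the assumed range:

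| SD | n = 50 | n = 65 |
|---|---|---|
| 0.5 | 0.079 | 0.053 |
| 0.8 | 0.188 | 0.157 |
| 1.0 | 0.240 | 0.210 |
| 1.2 | 0.278 | 0.251 |

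**Step 3. The analysis-section rule.** If a measure has true mean 3 and its sample mean must reach 4, the chance of passing at n = 50 is at most 4.2×10⁻⁵ in the five distributions, that is, below 0.0001. Requiring AIM and IAM both to pass cannot raise it.

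**Step 4. A lower-limit rule.** If the one-sided 95% lower limit must exceed 3, the observed mean must exceed 3 + 1.645·SD/√n. At n = 50 this is 3.12, 3.19, 3.23 and 3.28 for SD 0.5, 0.8, 1.0 and 1.2. At n = 65 it runs from 3.10 to 3.25. A programme with true mean 3.0 then passes about 5% of the time.

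**The case against.** The strongest objection is that the satisfaction sentence may not decide anything. The analysis section is where one looks for the operative rule. It sets acceptability by AIM and IAM at 4 and only reports satisfaction. This stands, and it limits the finding. A reader might infer that the pilot as a whole would call a programme with no net approval acceptable half the time. The article does not support that: the figure holds only if the satisfaction rule suffices alone, which is what its sentence literally says but what the analysis section does not confirm.

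Second, any cutoff applied to a point estimate is passed about half the time when the truth lies on it, and the recruitment, completion, FIM, AIM and IAM criteria are all of this kind. This also stands. Point-estimate criteria are common in pilots, so the missing confidence limit is secondary. What sets this rule apart is that its cutoff lies at the midpoint.

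Third, a floor at the midpoint can be defended as a lenient but prespecified judgement, and the earlier single-arm pilot reported highly positive feedback, so a true mean near 3 is not the expected case. Interviews and the reported means would also show a lukewarm response. These arguments lower the practical stakes, but they do not tell the reader which of the two rules applies.

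Fourth, a reader might put the pass rate of a slightly disliked programme at a quarter. That depends on the assumed SD. Averaging several imperfectly correlated ratings per patient would reduce the SD and move the figure towards the lower end of the range.

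**Conclusion.** The point holds in limited form. The satisfaction rule, as worded and taken alone, is met with probability 0.51 to 0.54 by a programme with true mean 3.0 (50 to 65 raters), and with probability of about 0.08 to 0.28 by one with true mean 2.9 (50 raters, SD 0.5 to 1.2). The first result hardly depends on the assumed ratings; the second depends on them strongly. If the AIM/IAM rule governs or both rules apply, a programme rated 3 on those instruments would pass with probability below 0.0001, assuming 1–5 scoring. The article leaves open which of these situations applies, and on either reading the ≥3 sentence needs correction: it is too weak if it decides, and misleading if it does not. Severity is minor. It bears on the acceptability conclusion only, not on the primary FDI comparison.

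**What to change.** Before satisfaction data are analysed, state in both sections which rule decides acceptability. There are two ways to do so:

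- Make the AIM/IAM rule decisive and satisfaction descriptive, by deleting the ≥3 sentence from the satisfaction item.
- Require both rules, and replace the cutoff in the satisfaction item with: *the one-sided 95% lower confidence limit of mean satisfaction (session-specific and overall, as now defined) exceeds 3*. This keeps the session-specific ratings in the measure.

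In either case, report the proportion of ratings of 1 or 2, so that a divided response is visible behind the mean.

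The cost is a sentence in each of two sections and no new data. The downside of the second option is that a programme rated just above the midpoint, with an observed mean below about 3.1 to 3.3 at 50 raters, would no longer be called acceptable. A clearly liked programme loses nothing. With true mean 3.75, SD 1.0 and 65 raters, the required mean is 3.20 and the standard error is 1.0/√65 = 0.124, so the margin is (3.75 − 3.20)/0.124, or about 4.4 standard errors, and the programme passes with probability of about 1.00.

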### Ethical Considerations

The study was approved by the CHOP IRB (IRB 22-020664; approval date April 21, 2023; most recent amendment #21 approved on May 8, 2025). The protocol was also reviewed by the National Institute of Arthritis and Musculoskeletal and Skin Diseases (NIAMS) at the NIH. Any further amendments to the study protocol will be communicated to the CHOP IRB and NIAMS at the NIH for formal approval.

Written informed consent will be obtained from all participants, as described in this protocol. All participants will provide informed consent by acknowledging that they have read and understood the consent form before randomization. Information about the study’s significance, purpose, procedures, risks, and benefits will be provided to all eligible patients during the consent process. Identifiable information will be collected from subjects and parent participants only to link the questionnaires and qualitative data from the interviews to the EMR data. Identifiable information linking individual subjects to their PHI (i.e., the master list) will be stored electronically in a Microsoft Excel file located on a secure research SAN drive for the duration of the study and will be maintained in keeping with CHOP policy. Research documents located on the SAN drive will be accessible only to members of the study team. Upon study completion, the database will be maintained in locked mode for a minimum of 3 years, as per regulatory guidelines. Data management procedures are included in our manual of operating procedures, which can be made available upon request.

Since the survey measures ask questions about mood, stressors, psychological symptoms, and feelings, this might put participants at risk for having negative thoughts and emotions. It is not likely that answering these survey measures will create additional distress beyond that which is already present, but research staff will offer referral for clinical services (for child or parent) for any reported distress warranting clinical attention. In addition, if during study participation, the study team discovers abuse or neglect or if threat to harm self or others occurs, they will follow established institutional procedures for mandatory reporting of this information and will provide referrals for appropriate clinical follow-up. We also have a data safety monitoring plan (DSMP) and a data safety monitoring board (DSMB). The DSMB consists of 4 members, who meet once a year to review study progress and safety or confidentiality concerns. In the unlikely event of an adverse outcome associated with this study protocol (eg, disclosure of patient information), it will be documented and discussed with the research team and promptly reported to the local IRB and study sponsor, if appropriate. Any serious adverse events will be reported to the local IRB and the DSMB within 48 hours and to the study sponsor.

